### Outcomes

The primary objective of this study is to evaluate the implementation of a new wearable on the surgical ward at Catharina Hospital Eindhoven. This will be achieved by assessing its usability, degree of implementation, and the workload for nursing staff. The primary outcome will be acceptability, specifically evaluating workload as measured by the Integrated Workload Scale (IWS). The IWS is a comprehensive tool that provides multidimensional descriptions and gradations of workload, ranging from “not demanding” to “work too demanding” on a 9-point Likert scale. This scale is suitable for both periodic assessment and real-time monitoring of tasks, with measurements conducted throughout the entire study period.

For secondary outcomes, the study will apply the framework of the taxonomy of implementation outcomes of Proctor et al [12], focusing on adoption, feasibility, appropriateness, predictive accuracy, and technical feasibility. Adoption will be measured by the Evidence-Based Practice Attitude Scale and the System Usability Scale, along with the amount of spot checks conducted in addition to the standard monitoring.

Feasibility will be evaluated by determining the extent to which health care employees can successfully implement the device, and by measuring the time required to perform and process manual spot checks or digital monitoring checks. Appropriateness will be assessed by examining the SNR and counting the number of (suspected) adverse events that occur during or result from the use of the wearable.

Additionally, the predictive accuracy for early detection of health deterioration and postoperative complications among patients will be evaluated through focus group discussions. Technical feasibility will involve analyzing the availability of data on the web platform, including monitoring time and the types and quantities of algorithm artifacts, such as low-quality data during the monitoring of photoplethysmography values.

Approximately 70 nurses from the surgical ward will participate in the study and complete the IWS. In addition, 10 nurses and 5 physicians will voluntarily join focus groups to conduct an in-depth evaluation of the new implementation. These focus groups, which will be established prior to the study’s commencement, will meet 3 times during the study period to discuss the progress of the study and share their experiences with the implementation. A structured analysis of fidelity, feasibility, and acceptability will be conducted by the focus group, and this information will be processed and objectified using a thematic analysis devised by Braun and Clarke [11].

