### Implementation Phase

Implementation of the device as the new standard of care for monitoring will be executed in 2 distinct phases to ensure a thorough evaluation and implementation of this monitoring system (Table 1).

During phase 1 (the initial phase; months 1-3), patients will continue to receive the current standard of care, which involves manual spot checks and MEWS measurements by nursing staff. Concurrently, all health care staff will receive training on the application, data interpretation, and protocol adherence concerning the solution to optimize the infrastructure before its implementation.

Following phase 1 (in month 4; the evaluation and validation period), the preimplementation phase will be evaluated. Predictive accuracy will be evaluated by comparing device data against clinical outcomes such as complications, intensive care unit transfers, or MEWS-triggered interventions using area under the receiver operating characteristic curve analysis.

In phase 2 (months 5-8), the wearable will become the primary tool for patient monitoring, supplemented by manual spot checks by nurses as needed. This phase aims to evaluate the integration into standard care.

During the whole study, every minute data are securely stored. During phase 2 of the study, 6 times a day, median values of the previous 4-hour window will be uploaded to the EHR. In case of signal loss or low-quality readings, the system generates flags, allowing for assessment of signal-to-noise ratio (SNR).

**Table 1 table1:** Psychometric properties and statistical analysis.

Objective	Instrument	Variable	Statistical test	Achievement criteria
Fidelity	SUS^a^	Continuous	Unpaired *t* test or Mann-Whitney *U* test	Fidelity achieved when protocol adherence is ≥95%
Acceptance	SC^b^/day	Continuous	Descriptive statistics	Acceptance achieved when ≥75% of nurses use the device regularly
Acceptance	SC/patient	Continuous	Descriptive statistics	Acceptance achieved when ≥75% of nurses use the device regularly
Acceptance	IWS^c^	Ordinal	1-way ANOVA	Acceptance achieved when ≥75% of nurses use the device regularly
Adoption	EBPAS^d^	Continuous	Repeated measures ANOVA	Adoption achieved when device use exceeds 70% by clinical staff
Appropriateness	SNR^e^	Continuous	Descriptive statistics	Adoption achieved when device use exceeds 70% by clinical staff
Appropriateness	ADE^f^	Continuous	Descriptive statistics	Appropriateness achieved with minimal ADEs

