Feasibility	Thematic analysis	Nominal	Braun and Clarke [11] thematic analysis	Feasibility achieved when 80% of clinicians can successfully implement the device
Time efficiency	Time measurement	Continuous	Descriptive statistics	Time efficiency achieved when nurses’ time spent on monitoring decreases by ≥20%
Predictive accuracy	MEWS^g^ and CREWS^h^	Nominal	AUROC^i^	Predictive accuracy achieved when AUROC ≥0.80

^a^SUS: System Usability Scale.

^b^SC: spot check.

^c^IWS: Integrated Workload Scale.

^d^EBPAS: Evidence Based Practice Attitude Scale.

^e^SNR: signal-to-noise ratio.

^f^ADE: adverse device event.

^g^MEWS: Modified Early Warning Score.

^h^CREWS: Continuous Remote Early Warning Score.

^i^AUROC: area under the receiver operating characteristic curve.

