## Results

Staff training was completed in October 2024, and full implementation is ongoing. Up to 150 participants intend to be enrolled in the study. Preliminary findings, including data on usability and workload, are expected by July 2025 (see details in Table 2).

**Table 2 table2:** Measurement timetable for psychometric properties.

Objective	Instrument	0^a^	1	2	3	4 (evaluation/validation)	5	6	7	8 (evaluation/validation)
Fidelity	SUS^b^						Q^c^			Q
Acceptance	SC^d^/day				AD^e^					AD
Acceptance	SC/patient				AD					AD
Acceptance	IWS^f^	Q			Q		Q	Q	Q	Q
Adoption	EBPAS^g^	Q			Q				Q	Q
Appropriateness	SNR^h^									AD
Appropriateness	ADE^i^									AD
Feasibility	Thematic analysis				FG^j^			FG		FG
Time efficiency	Time measurement		M^k^	M	M		M	M	M	M
Predictive accuracy	MEWS^l^ and CREWS^m^		M	M	M	AD and M	AD (and M)	AD (and M)	AD	AD

^a^Numbers 0-8 represent the study months, starting from baseline (month 0) through to month 8.

^b^SUS: System Usability Scale.

^c^Q: questionnaire.

^d^SC: spot check.

^e^AD: administered data.

^f^IWS: Integrated Workload Scale.

^g^EBPAS: Evidence Based Practice Attitude Scale.

^h^SNR: signal-to-noise ratio.

^i^ADE: adverse device event.

^j^FG: focus group.

^k^M: manual measurement.

^l^MEWS: Modified Early Warning Score.

^m^CREWS: Continuous Remote Early Warning Score.

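### Predictive accuracy is given two incompatible methods, and the 80% feasibility rule is paired with a qualitative instrument that yields no proportion

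*Protocol article*

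**What the plan says.** **Predictive accuracy.** The Outcomes section lists it as a secondary outcome and says that it "will be evaluated through focus group discussions". The Implementation Phase section describes something else: "Predictive accuracy will be evaluated by comparing device data against clinical outcomes such as complications", with transfers to intensive care and interventions triggered by MEWS as further examples, "using area under the receiver operating characteristic curve analysis". Table 1 names MEWS and CREWS as the instruments and sets the rule "Predictive accuracy achieved when AUROC ≥0.80". Table 2 (Results) fills this row only with manual measurements and administered data.

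**Feasibility.** Table 1 gives thematic analysis as both instrument and statistical method, with the rule "Feasibility achieved when 80% of clinicians can successfully implement the device". Table 2 schedules the row only as focus groups, in months 3, 6 and 8. The Outcomes section has the focus group carry out the analysis of feasibility and says that "10 nurses and 5 physicians will voluntarily join focus groups". About 70 nurses take part in the study.

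**The concern.** These are two separate defects, and both concern outcomes with an explicit pass mark.

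For predictive accuracy, two methods of different kinds stand in the same article. One is a patient-level discrimination statistic and the other is staff opinion. As the text stands, either could be reported under this outcome's name, and the choice could be made after the data are seen.

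For feasibility, the rule needs a numerator and a denominator, and the listed method supplies neither. Feasibility could be declared achieved with no defined proportion behind it. If the gap were filled by counting focus group members, the percentage would rest on 15 self-selected people while the rule speaks of clinicians in general.

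**Working it through.** The article derives no sample size or precision for either criterion, so there is no stated figure to reproduce.

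**A. Predictive accuracy: the places side by side**

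| Place | Method or data |
|---|---|
| Outcomes | Focus group discussion |
| Implementation Phase | Device data against clinical outcomes, AUROC |
| Table 1 | MEWS and CREWS, AUROC, pass mark 0.80 |
| Table 2 | Manual and administered data; no focus group entry |
| Outcomes, tasks of the focus group | Fidelity, feasibility and acceptability; predictive accuracy not listed |

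The AUROC is the probability that a randomly chosen patient with the event has a higher score than a randomly chosen patient without it. It needs a score and an observed outcome for each patient. Focus groups give neither, whatever their size or selection. One sentence therefore conflicts with the method, the criterion and the schedule, which agree with each other.

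**B. Feasibility: what a head count of the focus group would be worth**

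Inputs from the article: 10 nurses + 5 physicians = 15 members; pass mark 80%; 0.80 × 15 = 12.

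*Exact (Clopper-Pearson) 95% CI for x of n.* The lower limit is the 2.5% quantile of Beta(x, n − x + 1). The upper limit is the 97.5% quantile of Beta(x + 1, n − x).

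- 12 of 15: Beta(12, 4) gives 0.519 and Beta(13, 3) gives 0.957, so 52% to 96%.
- 15 of 15: the lower limit is 0.025^(1/15) = 0.782. Even complete success does not exclude a share below 80%.

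*Chance of meeting the rule if the 15 were a random sample with true share p.* P(X ≥ 12) is the sum over k = 12 to 15 of C(15, k) p^k (1 − p)^(15 − k). At p = 0.70:

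- k = 12: 455 × 0.7^12 × 0.3^3 = 0.170
- k = 13: 105 × 0.7^13 × 0.3^2 = 0.092
- k = 14: 15 × 0.7^14 × 0.3 = 0.031
- k = 15: 0.7^15 = 0.005
- Sum: 0.297 from unrounded terms

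| True share | P(at least 12 of 15) |
|---|---|
| 60% | 0.09 |
| 70% | 0.30 |
| 75% | 0.46 |
| 80% | 0.65 |

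*Comparison with a count over the ward.* The number of ward physicians is not given, so two denominators are shown.

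- 70 (nurses only): 56 of 70 = 80%, exact 95% CI 68.7% to 88.6%.
- 75 (assumed: 70 nurses and 5 physicians): 60 of 75 = 80%, exact 95% CI 69.2% to 88.4%. At a true share of 70%, the binomial chance of 60 or more is 0.035, against 0.297 with 15.

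None of these figures includes any effect of volunteering.

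**The case against.** The strongest defence on predictive accuracy is that the plan is clear in every place but one. The method, the pass mark and the timetable all point to patient data, and a single sentence is out of line. This stands, and it limits the point. A reader might infer that the AUROC threshold itself has been handed to 15 volunteers, or that a better-chosen group would cure the problem. The documents support neither reading. No place ties the 0.80 threshold to focus groups, and the obstacle is the type of data, not who was selected. The contradiction remains because the sentence sits in the section that defines the outcomes.

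On feasibility, the rule speaks of clinicians, and the Outcomes section speaks of health care employees without restricting them to focus group members. No place plans a count out of 15. A reader might infer that the focus group share will be reported as the ward's percentage, or that the volunteers will be enthusiasts. The first is a prediction, and the second goes beyond the stated fact that joining is voluntary. The criticism that remains is narrower: both tables name only a qualitative instrument for a percentage rule. The Outcomes section adds time measurement under feasibility, but time efficiency has its own row and its own rule of a 20% decrease, so it does not supply the missing proportion.

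The month 3 meeting comes before the device is the primary tool. That is not a defect, because meetings about progress and experience may begin early and the other two fall in phase 2.

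Finally, an article condenses a fuller protocol. That would excuse silence, but here the article states both conflicting methods and fixes the feasibility instrument in two tables.

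**Conclusion.** The point holds as two limited defects in secondary outcomes.

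1. The Outcomes sentence on predictive accuracy contradicts the Implementation Phase section, Table 1 and Table 2. Followed literally, it cannot produce the AUROC on which the outcome is judged. This rests on the text alone and has no numerical size.
2. The 80% feasibility rule has no listed instrument that yields a proportion. The figures (52% to 96% for 12 of 15; probability 0.30 of passing at a true share of 70%) show what the obvious stopgap would be worth, not what the article says will be done. They assume independent answers and random choice of members. The ward-wide comparison assumes a denominator of 70 or 75.

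The primary outcome, workload on the IWS, is untouched. The corrections are still worth making, because each outcome carries a success rule that the text as written cannot deliver.

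**What to change.** **Predictive accuracy.** In the Outcomes section, replace the focus group sentence with the AUROC analysis of the Implementation Phase section and Table 1. If staff views are wanted, say that the focus groups report only the perceived value of the device for early detection, with no bearing on the 0.80 criterion. Cost: one sentence.

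**Feasibility.** Decide the 80% rule on a countable measure, defined in advance, over all participating ward clinicians, and report it with an exact 95% CI.

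- One route is a success item added to the questionnaires already given to the approximately 70 nurses, and put to the ward physicians as well. Month 8 is a natural time, since Table 2 already places the IWS, EBPAS and SUS there. State how non-responders count.
- Another route is usage records, if they identify the staff member. The article describes stored patient vital signs and no staff-level log, so this is an assumption to check.

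Change the instrument in Table 1 and the entry in Table 2 to match. Keep the thematic analysis as explanatory evidence without a numeric threshold.

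Cost: one added item or one tabulation. The feasibility figure may be lower than a focus group would suggest. The measure must also be kept distinct from the adoption rule, which already uses device use above 70% by clinical staff; otherwise the two outcomes would largely repeat each other.

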### Statistical Analysis

Quantitative data will be analyzed using IBM SPSS Statistics (version 26.0). Descriptive statistics will be used to summarize categorical data (frequencies and percentages) and continuous variables (means and SD or medians and IQRs, depending on the distribution). Normality will be assessed using the Shapiro-Wilk test. Group comparisons will be made using *t* tests, ANOVA, Mann-Whitney *U*, or chi-square tests where appropriate. For repeated measures, linear mixed models or repeated measures ANOVA will be used. Qualitative data from focus groups will be coded and thematically analyzed following Braun and Clarke’s [11] approach.

### Ethical Considerations

This study involves human participants and has been approved by Medical Research Ethics Committees United (reference number W24.065). Written informed consent to participate will be obtained from all participants prior to inclusion in the study.

All data collected will be pseudonymized before analysis to protect participants’ privacy. Personal identifiers will be replaced with unique study codes, and the key linking codes to participant identities will be stored separately in a secure, access-restricted location. Only authorized study personnel will have access to this information.

Participants will not receive any financial compensation or other incentives for participation in this study. Participation is voluntary, and participants may withdraw at any time without any consequences for their care.

## Results

Staff training was completed in October 2024, and full implementation is ongoing. Up to 150 participants intend to be enrolled in the study. Preliminary findings, including data on usability and workload, are expected by July 2025 (see details in Table 2).

**Table 2 table2:** Measurement timetable for psychometric properties.

Objective	Instrument	0^a^	1	2	3	4 (evaluation/validation)	5	6	7	8 (evaluation/validation)
Fidelity	SUS^b^						Q^c^			Q
Acceptance	SC^d^/day				AD^e^					AD
Acceptance	SC/patient				AD					AD
Acceptance	IWS^f^	Q			Q		Q	Q	Q	Q
Adoption	EBPAS^g^	Q			Q				Q	Q
Appropriateness	SNR^h^									AD
Appropriateness	ADE^i^									AD
Feasibility	Thematic analysis				FG^j^			FG		FG
Time efficiency	Time measurement		M^k^	M	M		M	M	M	M
Predictive accuracy	MEWS^l^ and CREWS^m^		M	M	M	AD and M	AD (and M)	AD (and M)	AD	AD

^a^Numbers 0-8 represent the study months, starting from baseline (month 0) through to month 8.

^b^SUS: System Usability Scale.

^c^Q: questionnaire.

^d^SC: spot check.

^e^AD: administered data.

^f^IWS: Integrated Workload Scale.

^g^EBPAS: Evidence Based Practice Attitude Scale.

^h^SNR: signal-to-noise ratio.

^i^ADE: adverse device event.

^j^FG: focus group.

^k^M: manual measurement.

^l^MEWS: Modified Early Warning Score.

^m^CREWS: Continuous Remote Early Warning Score.

## Discussion

This study is expected to demonstrate that the implementation of continuous vital sign monitoring using the viQtor wearable device is feasible within a surgical ward setting. We anticipate that this technology will be perceived as acceptable and usable by health care professionals, and that its integration may contribute to a measurable reduction in perceived nursing workload. Importantly, by including continuous SpO₂ monitoring, the system may offer added clinical value in identifying early signs of postoperative deterioration.

While earlier studies have assessed the technical accuracy of wearable monitoring devices, relatively few have focused on their integration into clinical workflows. For instance, Breteler et al [8] validated a similar system in high-risk surgical patients, but implementation outcomes such as usability or staff adoption were not the focus. Bellomo et al [7] also examined automated advisory systems, but their routine use in general hospital wards remains uncommon.

Our study distinguishes itself by applying a structured implementation framework, specifically the revised Medical Research Council guidance [10] and the taxonomy of implementation outcomes of Proctor et al [12]. This approach allows us to assess whether the device not only works but also can be realistically adopted in daily practice.

A notable addition in our protocol is the continuous monitoring of SpO₂, a parameter that was lacking in earlier studies such as those involving a Healthdot device. Since respiratory complications are among the more frequent and severe postoperative issues, continuous SpO₂ tracking may enhance the early recognition of patient decline [4,6,13].

The study’s multidisciplinary design, combining clinical, technical, and implementation expertise could be seen as a strength. The use of validated instruments—including the IWS [14], Evidence-Based Practice Attitude Scale [12], and the System Usability Scale—ensures a structured and multidimensional evaluation.

Limitations of this study can be expected as well. As a single-center trial focusing on patients undergoing elective surgery, its findings may not be directly generalizable to other hospital departments or to emergency or critical care populations. Additionally, while the viQtor device captures data at regular intervals, data loss or reduced signal quality could occur. These technical aspects will be explored through SNR analysis and artifact tracking.
If implementation proves successful, the findings may support broader deployment across other wards or institutions. Future research could explore postdischarge remote monitoring or the integration of wearable data into clinical decision support systems, possibly enhanced by predictive algorithms.

Results will be shared internally within the hospital through clinical meetings and departmental presentations. Externally, we plan to present findings at national conferences and submit our results to peer-reviewed journals. Data will be made available upon reasonable request, and the implementation protocol may serve as a blueprint for similar projects in other hospitals.

## Abbreviations

CE: Conformité Européenne
EHR: electronic health record
EWS: Early Warning Score
IWS: Integrated Workload Scale
MEWS: Modified Early Warning Score
REQUEST: Remote Monitoring by viQtor Upon Implementation on a Surgical Department
SNR: signal-to-noise ratio
SpO₂: peripheral oxygen saturation
